#### Exposure and Outcome Definitions

Definitions of dietary intakes and CMDs are based on definitions used by the GBD [1,18]. In addition to the 15 dietary intakes used by the GBD, ultraprocessed food intake will be included where practicable given the increasing literature in the field linking this dietary exposure to a wide range of health outcomes [22-25]. In doing so, we will use the most widely adopted food classification system based on the purpose and extent of industrial food processing, Nova, to define ultraprocessed foods [20]. Furthermore, we will follow best practice guidelines when categorizing foods according to the Nova food classification system [26].

CMDs can be measured differently across epidemiological studies. They are most commonly assessed using self-reported symptom scales with cutoffs for diagnosis, from medical records, or using diagnostic interviews. Multimedia Appendix 1 outlines some commonly used tools and their recommended cutoffs for identifying symptoms of depression and anxiety. The sensitivity, specificity, and diagnostic accuracy of these tools largely depend on the population. When undertaking meta-analyses, we may conduct a sensitivity analysis to determine if the magnitudes of associations change based on exposure and outcome measurement or ascertainment type.

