#### Estimating Risk Ratios, Odds Ratios, and Hazards Ratios

Each study is required to use risk ratios (estimated by Poisson regression with robust SE) as the primary means of assessing the association of dietary intake with CMDs. Risk ratios are based on incident cases, and so models will need to exclude participants with depression or anxiety at baseline. Furthermore, to determine incident risk, studies must have dietary exposures at baseline and depression, or anxiety measured at a subsequent time point. Where the estimation of a risk ratio is not possible (refer to Figure 2), for example, where the total number of people exposed at baseline is not available (such as for retrospective or case-control studies) [29], odds ratios are estimated using standard logistic regression techniques. Where only time-to-event data are available, hazard ratios are used, estimated by a Cox proportional hazards model. For rigor, all effect estimates will be accompanied by a 95% CI and exact *P* value [30].

Models can be fitted using any statistical analysis software, including R (R Core Team), SAS/STAT (SAS Institute Inc), Stata (StataCorp LLC), and SPSS (IBM Corp). Before fitting the relevant models, Member studies must assess model assumptions. Should any model assumptions be violated, an alternate approach to analysis may be selected. For example, the nonlinearity of continuous variables should be investigated, and transformations or nonlinear models fitted where necessary. Similarly, should any of the assumptions of Cox proportional hazards models be violated, alternative strategies will be deployed to account for these violations.

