In addition to the models listed above, the following subgroups shall be fitted separately for each exposure-outcome pairing, where data allows: (1) sex, (2) age, (3) year (for longitudinal studies with multiple waves of follow-up), (4) country (for multicenter studies), and (5) all symptom scales and diagnostic measures (for studies with depression and anxiety measured via multiple measures. For age, studies should explore the relationship between the risk factors and mental disorders with age to see if a continuous measure is appropriate. Where a continuous measure is not appropriate, studies should generate appropriate age categories for their dataset by inspecting the frequency of outcomes by age groups. As a guide, the GBD currently uses 0-6 days (early neonatal), 7-27 days (late neonatal), 28-365 days, 1-4 years, 5-9 years, then 5-year intervals from 10-95 [31].

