### Sensitivity Models

#### Multiple Testing

Given the need for multiple models to be fitted within each study, the GLAD Taskforce recommends a *P* value adjustment procedure, such as the Simes method, to minimize the chance of a type 1 error and determine whether multiple testing may be influencing results [32]. This should be applied to all models in a study where multiple models are required.

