Risk factors for CMDs in the GBD are currently limited, and so, the inclusion of these additional lifestyle risk factors will represent a significant expansion in the scope of the GBD, which will have global policy implications. Our work builds upon the previous efforts of studies that have successfully integrated novel risk factors for CMDs in the GBD. For example, bullying victimization has been successfully incorporated into the GBD as a level 3 risk and is now routinely integrated into GBD papers [67,68]. By emulating the successful integration of these other risk factors into the GBD, our comprehensive, collaborative approach to harmonized statistical analyses across multiple, internationally renowned epidemiological cohorts has the potential to establish a basis for evidence-backed preventive strategies focused on lifestyle risk factors to reduce the burden of CMDs. Furthermore, by operationalizing the definitions to be in line with the GBD, which are used to inform global policy guidelines, and by capturing data from different regions, sexes, and ages, these results have the potential to bring benefits to individuals and communities on a global scale.

There is substantial observational [69-71], intervention [72-76], and meta-analytical [5,77-79] evidence linking these lifestyle factors to CMDs globally, which suggests that lifestyle factors are potentially suitable (and importantly, modifiable) preventive strategies. This has been recognized by the Royal Australian and New Zealand College of Psychiatrists, with lifestyle treatments integrated into the recent clinical practice guidelines for mood disorders, including depressive disorders [9]. A 2020 meta-review identified that targeting lifestyle variables like physical activity and smoking can be used effectively in the prevention and treatment of CMDs [5]. However, there was less evidence for the role of targeting diet in preventing CMDs, particularly as defined by international policy guidelines or as per the GBD framework. In order to incorporate additional lifestyle factors into guidelines globally, we need comprehensive epidemiological evidence, with a particular focus on dietary risks. The GLAD project will address previous methodological limitations through global collaborations and following a rigorous methodological framework informed by the GBD.

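### Sex and age subgroups are required as separate models with their own P values, but no study-level contrast between subgroups is specified and the results are not labelled exploratory

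*Protocol article*

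**What the plan says.** All references are to the protocol article.

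- **Estimating Risk Ratios, Odds Ratios, and Hazards Ratios (subgroups).** The article requires that "the following subgroups shall be fitted separately for each exposure-outcome pairing, where data allows: (1) sex, (2) age, (3) year". Country (multicenter studies only) and the different outcome measures complete the list. For age, studies first examine whether a continuous measure is suitable. If not, they form categories after looking at how often the outcome occurs by age.
- **Same section (reporting).** "all effect estimates will be accompanied by a 95% CI and exact *P* value".
- **Exposure and Outcome Definitions.** "In addition to the 15 dietary intakes used by the GBD, ultraprocessed food intake will be included where practicable". With depression and anxiety as outcomes, this gives 30 required pairings.
- **Multiple Testing.** The Taskforce "recommends a *P* value adjustment procedure, such as the Simes method, to minimize the chance of a type 1 error", and adds: "This should be applied to all models in a study where multiple models are required".
- **Future Directions: Meta-Analyses.** A phase 3 meta-regression will look at how risk varies with demographic factors, under a separate protocol.

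No section specifies an interaction term, a heterogeneity test or any other between-subgroup contrast for the member studies. The article uses the word exploratory only for discretionary additional analyses (Covariates and Confounders), not for these required subgroups.

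**The concern.** A P value in women and another in men each test whether that stratum's association is zero. Neither tests whether the two associations differ. When two such P values are all that is laid out, the natural comparison is significant in one sex and not in the other. That pattern is common by chance when the effect is identical in both.

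Member studies publish their own papers before phase 3 begins, so this is how subgroup results will first appear. The subgroups matter to the project: Anticipated Impact says that "by capturing data from different regions, sexes, and ages, these results have the potential to bring benefits to individuals and communities on a global scale". Age categories chosen after inspecting the data add a further reason for an exploratory label.

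**Working it through.** The article gives no power, effect size, event rate or significance threshold, so it has no figure to reproduce. What follows is an illustration.

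**From the article:** 15 exposures x 2 outcomes = 30 pairings, hence 60 sex-stratum models (32 and 64 with the optional ultraprocessed food exposure).

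**Assumed:** two-sided 0.05 Wald tests; two equal, independent sex strata; the same true effect in both; independent pairings; whole-sample power of 50%, 80% or 90%, or no effect.

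**Step 1, power in one stratum.** The whole-sample mean Z is d = 1.96 + z(power). Each half-sample has mean Z of d/√2. At 80% power, d = 1.96 + 0.84 = 2.80 and d/√2 = 1.98, so the stratum rejection probability is p = 0.508.

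**Step 2, disagreement on significance.** P(exactly one stratum significant) = 2p(1 − p). At 80% power this is 2 x 0.508 x 0.492 = 0.500, or 30 x 0.500 = 15.0 pairings.

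| Whole-sample power | p per stratum | Disagreement | Expected of 30 |
|---|---|---|---|
| no effect | 0.050 | 9.5% | 2.85 |
| 50% | 0.283 | 40.6% | 12.2 |
| 80% | 0.508 | 50.0% | 15.0 |
| 90% | 0.630 | 46.6% | 14.0 |

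A 30:70 split gives 42.2%, 54.9% and 54.0% at the three power levels.

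**Step 3, the recommended adjustment.** The Simes method leads to more than one step-up procedure, so two were simulated over the 60 stratum P values (3,000 runs):

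| Scenario | Unadjusted | Benjamini-Hochberg | Hochberg |
|---|---|---|---|
| no effect | 2.85 of 30 | 0.06 | 0.05 |
| common effect, 80% power | 15.0 of 30 | 13.3 | 5.0 |

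Adjustment nearly removes the disagreement when there is no association, but not when there is a common one. The Introduction hypothesizes associations.

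**Step 4, a direct contrast.** With no true modification, one interaction test per pairing at 0.05 flags 30 x 0.05 = 1.5 pairings, whatever the main effect. Unadjusted, the chance of at least one false flag is 1 − 0.95^30 = 0.785, so these tests need the multiplicity step too. The 1.5 is an unadjusted figure and should be compared with the 15.0. Adjustment would lower it further.

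**Step 5, precision of the contrast.** With equal strata, each stratum SE is √2 times the whole-sample SE. The SE of the difference in log risk ratios is √(2 + 2) = 2 times the whole-sample SE.

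**The case against.** **Nothing quoted is wrong in itself.** Separate models are a legitimate way to obtain stratum estimates, and Results says study-level estimates are generated for pooling. For disjoint strata the ratio of risk ratios can be computed from the two reported estimates. This stands, and it is why the separate estimates should be kept. It also shows how little the missing contrast would cost.

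**An article may leave such detail to a fuller plan.** This carries limited weight here. Results tells member studies to follow the analysis plan set out in this paper, and the paper does fix a subgroup method.

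**The plan already covers part of the ground.** It recommends adjustment across all models, allows age to be treated as continuous, and plans a meta-regression. All three are true. But adjusting stratum P values does not test their difference, no exposure-by-age term is named, and the meta-regression comes after the member papers, in a protocol still to be created.

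**Country hardly applies.** It is limited to multicenter studies, and each of the 18 cohorts in Table 4 lists one country. A footnote to Table 3 allows for unlisted studies, but on what is shown the point concerns sex and age.

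**A stronger reading is tempting:** that the plan tells studies to infer effect modification from significance in one stratum and not another, or that it will generate false subgroup claims. The article does not support this. It states no such rule and no significance threshold, and what authors will conclude is a prediction.

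**Conclusion.** The point holds at member-study level and in a limited form. The plan requires separate sex and age models with P values, specifies no contrast between them and does not label them exploratory. This invites differences in significance to be read as effect modification, though it does not prescribe that reading. A reader might also infer that the project never assesses variation by demographic factors; the phase 3 meta-regression rules that out.

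Under the illustrative assumptions at 80% power, 5.0 to 13.3 of 30 sex pairings would still disagree on significance after adjustment. If there is no association, almost none would. These counts assume a real, common effect in all 30 pairings, independence between pairings, and adjustment over the 60 sex-stratum models only. They show the scale of the problem and do not predict any cohort's results. The change is worth making because it is nearly free.

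**What to change.** In the subgroup paragraph of Estimating Risk Ratios, Odds Ratios, and Hazards Ratios:

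1. Keep the separate stratum estimates with CIs for GBD pooling. Their P values can stay, since the section requires them for every estimate.
2. For each pairing, add the ratio of risk ratios between subgroups with 95% CI and P value. For disjoint strata, take it from the difference in log estimates, with SE = √(SE₁² + SE₂²). Otherwise use an exposure-by-subgroup product term, or exposure-by-age where age is continuous. Where odds or hazard ratios are used, take the corresponding ratio.
3. Include these contrasts in the step described under Multiple Testing.
4. Label subgroup results exploratory, and state that effect modification is judged only from the contrast and not by comparing stratum P values.
5. Pass the within-study contrasts to phase 3 so that they can be pooled.

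**Cost.** No new data are needed, only one derived estimate or model term per comparison and a few sentences of text. If a product-term model is used without also letting the confounder effects vary by subgroup, it imposes common confounder effects, which the separate fits do not; the difference-of-logs route avoids this. The contrasts will be imprecise in the smaller cohorts (Table 4 goes down to a maximum of 639 participants), so fewer subgroup differences will be claimed.

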**Figure 2 figure2:**
[figure not shown]
The types of ratio measures that can be obtained from binary outcome data. Odds ratios will be estimated using logistic regression, risk ratios will be estimated using Poisson regression with robust SE, and hazard ratios will be estimated using Cox regression.

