## Results

As of August 2024, 18 longitudinal studies have agreed to participate in the GLAD project (Table 3). These studies have sample sizes ranging from 639 participants to 171,000 participants (Table 4).

The GLAD project comprises 3 essential phases, which will be repeated for other lifestyle exposures of interest: (1) conducting a systematic search to identify relevant studies and recruit study leads to contribute data, (2) generating estimates of study-level associations of dietary risk factors with CMDs using harmonized data analysis protocols developed by the GLAD Taskforce and approved by the GBD, and (3) pooling results from each study to provide the GBD with robust estimates to calculate the diet-CMD risk-outcome pairs in the first instance.

As of August 2024, phase 1 of the GLAD project has been completed, and phase 2 is due for completion in early 2025, at which time phase 3 of the GLAD project is due to begin (Figure 3).

Phase 1 includes searching for and recruiting studies with suitable data, harmonizing data definitions by ensuring member studies use the exposure definitions listed in Table 1 and the outcome definitions listed in Table 2, and harmonizing data analyses by ensuring member studies follow the statistical analysis plan presented in this paper.

**Table 3 table3:** Details of the ethics approval for currently listed member studies^a^.

Study name	Ethics review board
The African-PREDICT^b^ study [44]	North West Department of Health and Health Research Ethics Committee of the North-West University.
Child to Adult Transition Study [45]	Royal Children’s Hospital Human Research Ethics Committee.
Dunedin Study [46]	Health and Disability Ethics Committee, Ministry of Health.
Environmental Risk (E-Risk) Longitudinal Twin Study [47,48]	Joint South London and Maudsley and the Institute of Psychiatry Research Ethics Committee.
Fragility in the Elderly Lombardy Study [49]	Ethics committee of the University of Pavia.
Geelong Osteoporosis Study [50]	Barwon Health Human Research Ethics Committee.
Health4Life [51,52]	University of Sydney, NSW^c^ Department of Education, University of Queensland, Curtin University, and relevant Catholic school ethics committees.
Healthy Life in an Urban Setting [53]	Ethical Review Board of the Academic Medical Center Amsterdam.
Longitudinal Aging Study Amsterdam [54]	Medical ethics committee of the VU University Medical Center.

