Lothian Birth Cohort 1936 [55,56]	Multi-Centre Research Ethics Committee for Scotland and Lothian Research Ethics Committee.
Melbourne Collaborative Cohort Study [57]	Cancer Council Victoria's Human Research Ethics Committee.
Moli-sani Study [58]	Ethical committee of the Catholic University in Rome.
Netherlands Study of Depression and Anxiety [59]	Medical Ethical Committee of the Vrije Universiteit (VU) Medical Centre and medical ethical committees of the participating universities.
Northern Ireland Cohort of Longitudinal Ageing [60]	School of Medicine, Dentistry and Biomedical Sciences of Queen’s University Belfast.
NutriNet Brasil [61]	Ethics committee of the School of Public Health from São Paulo University
NutriNet-Santé [62]	Ethics committee of the French National Institute for Health and Medical Research and by the National Commission on Informatics and Liberty.
Piccolipiù/Piccoli+/Piccolipiù in Forma [63]	Ethics committees of the Local Health Unit Roma E (management center), of the Istituto Superiore di Sanità (National Institute of Public Health) and of each local center.
REgistre GIroní del COR [64,65]	Institut Municipal d'Assistencia Sanitaria Ethics Committee

^a^Additional studies may be participating in or providing data for the GLAD project and not be listed here.

^b^African-PREDICT: African Prospective study on the Early Detection and Identification of Cardiovascular disease and Hypertension.

^c^NSW: New South Wales.

**Table 4 table4:** Overview of the studies participating in the GLAD^a^ project.

Study name	Study location	Maximum possible sample size^b^, n	Age range
The African-PREDICT^c^ Study [44]	South Africa	1202	20-30 years
Child to Adult Transition Study [45]	Australia	1239	Older than 8 years
Dunedin Study [46]	New Zealand	1037	0-45 years
Environmental Risk (E-Risk) Longitudinal Twin Study [47,48]	United Kingdom	2232	0-18 years
Fragility in the Elderly Lombardy Study [49]	Italy	639	Older than 65 years
Geelong Osteoporosis Study [50]	Australia	1518	Older than 30 years
Health4Life [51,52]	Australia	6639	11-13 years; 14-17 years
Healthy Life in an Urban Setting [53]	The Netherlands	24,789	18-70
Longitudinal Aging Study Amsterdam [54]	The Netherlands	3805	55-85 years
Lothian Birth Cohort 1936 [55,56]	United Kingdom	1091	Older than 60 years
Melbourne Collaborative Cohort Study [57]	Australia	41,500	Older than 40 years
Moli-sani Study [58]	Italy	24,325	Older than 35 years

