Netherlands Study of Depression and Anxiety [59]	The Netherlands	3348	18-65 years
Northern Ireland Cohort of Longitudinal Ageing [60]	United Kingdom	8500	Older than 50 years
NutriNet Brasil [61]	Brazil	109,245	Older than 18 years
NutriNet-Santé [62]	France	171,000	Older than 18 years
Piccolipiù/Piccoli+/Piccolipiù in Forma [63]	Italy	3328	0-4 years
REgistre GIroní del COR [64,65]	Spain	11,158	Older than 26 years

^a^GLAD: Global burden of disease Lifestyle And mental Disorders.

^b^Maximum possible sample size refers to the largest reported sample size from study publications, study websites study protocol, or profile papers. The actual sample size to be included in the GLAD project may vary.

^c^African-PREDICT: African Prospective study on the Early Detection and Identification of Cardiovascular disease and Hypertension.

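### The required models do not call for standard errors that allow for clustered sampling, although a twin cohort and an apparently school-recruited cohort are members

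*Protocol article*

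**What the plan says.** The section Estimating Risk Ratios, Odds Ratios, and Hazards Ratios sets the primary analysis: "Each study is required to use risk ratios (estimated by Poisson regression with robust SE) as the primary means of assessing the association". Where a risk ratio cannot be obtained, "odds ratios are estimated using standard logistic regression techniques", and time-to-event data go to a Cox model. The Figure 2 legend repeats this: "risk ratios will be estimated using Poisson regression with robust SE, and hazard ratios will be estimated using Cox regression". The same section requires that "all effect estimates will be accompanied by a 95% CI and exact *P* value".

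No cluster unit, cluster-robust variance, GEE or mixed model is mentioned anywhere in the article. The Results section says that members are held to the analysis plan set out in this paper.

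Two listed members bear on this:
- The E-Risk study is a twin study by name, with a maximum n of 2232 (Table 4).
- Health4Life covers ages 11-13 and 14-17, with a maximum n of 6639 (Table 4). Its approving bodies in Table 3 include a state education department and "University of Queensland, Curtin University, and relevant Catholic school ethics committees". The article does not state how pupils were recruited or how many schools took part.

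**The concern.** In a Poisson model for a binary outcome, the ordinary robust SE corrects the variance that the Poisson assumption gets wrong. It does not correct for correlation between participants. Model-based logistic and Cox SEs assume independence outright. Twins plausibly share both diet and risk of depression or anxiety, and pupils of one school plausibly share a food environment and some outcome risk. When exposure and outcome are both positively correlated within clusters, participant-level SEs for the slope are too small.

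Members publish their own results, each with the required confidence interval and P value. An SE that is too small therefore matters in the member's own paper, whatever that study later weighs in the pooled estimate. Phase 3 also takes the phase 2 SEs as input. Correcting them afterwards would need within-cluster correlations that members are not asked to report. Since some members may cluster their SEs and others may not, the analysis would not be harmonized on this point.

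**Working it through.** The article gives no intraclass correlation, cluster size, number of schools or SE, so there is no figure of its own to reproduce. Every correlation, number of schools and between-study SD below is an assumption.

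**Formula.** For a regression slope with clusters of size m and within-cluster correlations ρx (diet) and ρy (outcome), the design effect is DEFF = 1 + (m − 1)·ρx·ρy. The correct SE is √DEFF times the participant-level SE. A nominal 95% interval then covers 2Φ(1.96/√DEFF) − 1.

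**Twins.** m = 2, at most 2232/2 = 1116 pairs (assuming all are complete pairs), ρx 0.3 to 0.7, ρy 0.1 to 0.5.
- Low end: 1 + 0.3 × 0.1 = 1.03; √1.03 = 1.015; coverage 94.7%.
- High end: 1 + 0.7 × 0.5 = 1.35; √1.35 = 1.162; coverage 90.8%.
- Ceiling, both correlations 1: DEFF 2, SE ratio 1.41, coverage 83.4%.

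**Schools.** m = 6639/J with J = 40 to 100 schools, ρx 0.01 to 0.10, ρy 0.01 to 0.05.
- Low end, J = 100, m = 66.4: 1 + 65.4 × 0.01 × 0.01 = 1.007; SE ratio 1.003; coverage 94.9%.
- High end, J = 40, m = 166: 1 + 165 × 0.10 × 0.05 = 1.825; SE ratio 1.351; coverage 85.3%.

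**Simulation check.** Poisson regression, 20% outcome, no true effect, 1000 runs for twins and 500 for schools. Outcome correlations are on the latent scale, so those of the yes/no outcome are smaller.

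| Design | ρx, latent ρy | Empirical SD | Ordinary robust SE (coverage) | Cluster-robust SE (coverage) |
|---|---|---|---|---|
| 1116 pairs | 0.6, 0.6 | 0.0452 | 0.0425 (93.5%) | 0.0469 (95.9%) |
| 1116 pairs | 0.4, 0.4 | 0.0435 | 0.0423 (94.3%) | 0.0442 (95.6%) |
| 70 schools × 95 | 0.10, 0.05 | 0.0273 | 0.0245 (92.2%) | 0.0272 (95.0%) |
| 70 schools × 95 | 0.05, 0.05 | 0.0260 | 0.0246 (94.4%) | 0.0261 (95.2%) |

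Empirical SD over ordinary robust SE is 1.06, 1.03, 1.11 and 1.06, in row order. The Monte Carlo SE of coverage is √(0.05 × 0.95/1000) = 0.7 percentage points for twins and √(0.05 × 0.95/500) = 1.0 for schools. The shortfalls at 93.5% and 92.2% exceed twice that error. Those at 94.3% and 94.4% do not.

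**Pooling.** The two cohorts hold 2232 + 6639 = 8871 of 416,595 maximum participants across Table 4, or 2.1%. Weights are 1/(v + τ²), with v assumed to be 1/(0.1·n) per SD of exposure, and DEFF 1.35 for twins and 1.5 for schools. The table shows each weight before and after allowing for clustering.

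| τ | Twin cohort | School cohort |
|---|---|---|
| 0 (common effect) | 0.54% to 0.40% | 1.59% to 1.07% |
| 0.05 | 3.7% to 3.1% | 6.5% to 5.5% |
| 0.10 | 5.0% to 4.6% | 6.3% to 6.0% |

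**The case against.** A reader might infer that the plan prescribes independence for its primary model. It does not: a cluster-robust sandwich SE is a robust SE, so a member that clusters on family or school complies as written. That stands. The charge is that clustering is not required for the risk ratio, and that the default SEs of the logistic and Cox models leave it out.

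The article also obliges members to assess model assumptions and lets them choose another approach if one fails. This gives a careful investigator a route. However, the choice is optional, and the examples given are nonlinearity and the Cox assumptions, not independence. The meta-analysis section also excludes papers that deviate substantially from the described methods, which gives members a reason to stay with the default.

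It can be said that variance detail belongs in each member's own analysis, or in the registration, which is not shown. That has limited force. The article calls itself the plan that members follow, and it goes down to cutoffs for Cook's distance and DFBETA.

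The size is uncertain, and some features pull it down. Table 4 gives maxima, and "The actual sample size to be included in the GLAD project may vary". Excluding baseline cases and using complete cases will break some twin pairs. Adjustment for age, sex and socioeconomic status may absorb some of the shared variation. The calculations above include none of these. School recruitment is itself an inference from the ethics bodies.

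A reader might also infer serious over-weighting in the meta-analysis. The documents do not support that: the cohorts are a small share of participants, pooling is by random effects, and its details are left to a separate protocol.

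**Conclusion.** The point holds as a gap in how the required models are specified, not as an error in what they state. A listed twin cohort, and very probably a school-recruited one, fall under models with no instruction on within-cluster correlation. A member using participant-level SEs would report intervals that are too narrow wherever diet and outcome both correlate within clusters.

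The degree is not known from the documents. It runs from negligible at low correlations to the upper ends shown above, about 16% on the SE for twins and 35% for schools, and in the moderate simulated settings coverage was close to nominal. It would be too strong to state as fact that these cohorts' intervals are too narrow. Any effect on pooled weights is small. The change is worth making because it protects each member's own inference and costs almost nothing.

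**What to change.** Add one clause to the section Estimating Risk Ratios, Odds Ratios, and Hazards Ratios: wherever participants were sampled in clusters, the Poisson, logistic and Cox models must use cluster-robust SEs at the sampling unit (such as family or school), or a GEE or mixed model at that level. Have members report the unit used and the number of clusters, so that phase 3 can see how each SE was obtained. Make the Figure 2 legend agree.

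With cluster-robust SEs the point estimates do not change. With GEE or mixed models they may shift slightly. The cost is slightly wider confidence intervals for the affected members. Members with unclustered samples are not affected.
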